### Study Design

In this multicenter, open-label, prospective, and cross-sectional study, patients will be evaluated for DED using the DEA01 (*test method*). A physician will then provide a DED diagnosis based on 2016 Asia Dry Eye Society criteria [20] (*standard method*). To ensure that the *test method* will not affect a patient’s treatment plan, the physician will make a diagnosis using only *standard method* results without reviewing *test method* results. A minimum number of 220 patients will be enrolled, with patients allocated into a DED group or a non-DED group based on the diagnosis obtained using the *standard method*. The study design is shown in Figure 2.

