### Primary Outcome

The primary outcome will be the sensitivity and specificity of the *test method* for DED diagnosis, compared with the *standard method*. Sensitivity and specificity will be calculated based on the diagnostic results of the 2 methods. In the *test method*, an app-based J-OSDI total score ≥13 measured using the DEA01 and an MBI score greater than the cutoff value based on the secondary outcome (5) will be considered DED positive. In the *standard method*, a paper-based J-OSDI total score ≥13 and TFBUT ≤5.0 seconds will be considered DED positive.

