### Sample Size and Statistical Analyses

In total, the enrollment of a minimum number of 220 study patients will be required. The CI for the sensitivity and specificity of the *test method* is set at ±10%. It is possible to calculate a sample size and a CI (a margin of error) using the following formula [52]:

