**(2)**

Therefore, the minimum sample size will be 100 patients in each group. To meet the minimum required number of patients in each group, the target total number of patients will be set at 110 for each group, assuming a 10% exclusion rate due to missing data.

For the primary end points, the sensitivity and specificity of DED diagnosis using the DEA01 will be calculated using ROC curve analysis with the cutoff value for the app-based MBI in the *test method*. This cutoff value will be calculated using ROC curve analysis [31]. The ROC curve will show sensitivity (positive rate) on the vertical axis and 1-specificity (false positive rate) on the horizontal axis, and the plots will be connected using straight lines. The point at which the sensitivity and specificity for DED diagnosis using the app-based MBI will be maximized and will be set as the cutoff value for MBI [31].

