The secondary outcomes of the overall concordance rate, positive/negative predictive value, and positive/negative likelihood ratio will be calculated by comparing the DED diagnosis results from the *test method* with the results from *standard method* in a mixed matrix. The diagnostic performance of DEA01 will be evaluated through calculating the area under the ROC curve plotted from the sensitivity and specificity of the *test method*. The substitutability of MBI measurement for TFBUT measurement in DED diagnosis will be assessed using ROC curve analysis and through calculating the area under the ROC curve, using the cutoff value of the app-based MBI for TFBUT ≤5 seconds. The internal consistency of the app-based J-OSDI will be evaluated using factor analysis and Cronbach α coefficient, with α>0.70 considered an acceptable range [53]. Correlation and consistency will be evaluated using Pearson or Spearman correlation coefficients, an intraclass correlation coefficient, and Bland-Altman analysis. In each patient group, study patients’ backgrounds will be analyzed using a 2-tailed unpaired *t* test for continuous variables and a chi-square test for categorical variables. If a continuous variable does not clearly follow a normal distribution, it will be appropriately transformed to a logarithm and aggregated with the mean and SD or the median and IQR will be used as descriptive statistics. The operability and usability of the DEA01 will be evaluated in each group using the average score of the 5-point Likert scale responses to the operability and usability questions and the number of patients who answered better or worse than neutral using 2-tailed unpaired *t* and chi-square tests. For safety assessment, the frequency and rate of adverse events will be calculated for each group, and between-group comparisons will be performed using Fisher exact probability or chi-square tests.

A 2-sided level of significance will be set at 5%, and the confidence coefficient will be set at 95%, unless otherwise specified. Missing value completion will not be performed.

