The DEA01 is used to help assess subjective symptoms and collect objective findings through OSDI administration and MBI measurements, respectively. The reliability and validity of the MBI and OSDI in a remote setting to facilitate DED diagnosis have been previously shown through a previous DEA01 app designed for DED research, namely, DryEyeRhythm [31,32]. Additionally, discrepancies between results obtained from the standard paper-based OSDI and app-based OSDI have been previously shown to be acceptable [32]. Our prior study utilized the MBI cutoff derived from a slit-lamp microscopy–based MBI study [26]. This study aims to establish an MBI cutoff for smartphone app-based diagnosis assistance for DED. The establishment of an optimal MBI cutoff value will enable more robust and reliable app-based remote DED diagnosis assistance through the use of the DEA01.

In this study, the diagnostic performance utilizing the app-based MBI as a proxy for the standard TFBUT will be evaluated using the DEA01. TFBUT reflects tear film stability and homeostasis, acting as a critical component of DED diagnosis. However, it requires specialized tools and materials, including fluorescein dye and slit-lamp microscopy. Moreover, the invasive nature of the examination disrupts the in vivo status of the tear film and the ocular surface [20-23]. Some studies have shown that fluorescein dye results are not consistently reproducible and that the dye may negatively affect the stability of the tear film [57-59]. The MBI has been shown to have a positive correlation with TFBUT [26], suggesting that the MBI can be used as a noninvasive, nonintrusive metric to substitute for TFBUT. An online screening test, based on a patient’s self-measurement of the time from stopping blinking to feeling discomfort, has shown the utility of screening for DED detection [26,60]. However, the DEA01 may be more objective as it automatically measures the MBI using the sensors of a smartphone camera and allows for the evaluation of DED symptoms using the J-OSDI questionnaire. This study seeks to assess the viability of replacing TFBUT with app-based MBI measurements, which may enable remote, noninvasive, and nonintrusive diagnosis assistance concerning DED.

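### The primary sensitivity and specificity are read at an MBI cutoff chosen to maximise them in the same patients, so each is overstated by about 1 to 4 points and nominal 95% intervals under-cover

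*Protocol article*

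**What the plan says.** Under Primary Outcome, a patient is positive by the test method if the app-based J-OSDI total is at least 13 and the MBI is "greater than the cutoff value based on the secondary outcome (5"). Secondary outcome 5 is the MBI cutoff for diagnosing DED against the standard method, to be found by ROC analysis in this study.

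Sample Size and Statistical Analyses gives the selection rule: "The point at which the sensitivity and specificity for DED diagnosis using the app-based MBI will be maximized" is set as the cutoff. The same paragraph says that the primary sensitivity and specificity are calculated with it. The Discussion confirms that establishing an app-based cutoff is an aim of the study, and notes that earlier work relied on an external one: "Our prior study utilized the MBI cutoff derived from a slit-lamp microscopy–based MBI study".

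On precision, the CI for sensitivity and specificity "is set at ±10%. It is possible to calculate a sample size and a CI (a margin of error") by a formula that is not legible in the text at hand. The result is that "the minimum sample size will be 100 patients in each group", and "the target total number of patients will be set at 110 for each group, assuming a 10% exclusion rate due to missing data". The general convention is: "A 2-sided level of significance will be set at 5%, and the confidence coefficient will be set at 95%, unless otherwise specified".

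The article describes one cohort. It mentions no cutoff fixed in advance, no separate derivation sample and no correction for choosing the cutoff on the evaluation data.

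**The concern.** A cutoff picked because it looks best in a sample will, on average, look better there than in new patients. Two errors add up: the observed maximum of the ROC criterion sits above the true maximum, and the chosen cutoff performs somewhat below the truly best one. Sensitivity and specificity reported at that point are therefore optimistic, and an interval that treats the cutoff as given in advance is centred too high and ignores the selection.

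At stake is the primary result of an app intended for later remote use, where accuracy would be expected to fall somewhat short of the published figures. The limitations paragraph of the Discussion covers patient selection and examination order but not this. The margin-of-error calculation behind the sample size does not mention that the cutoff is estimated.

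**Working it through.** **1. The plan's own figure.** Inputs from Sample Size and Statistical Analyses: half-width d = 0.10, 95% confidence (z = 1.96). The article gives no expected sensitivity or specificity, so the worst case p = 0.5 is assumed.

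n = z²p(1−p)/d² = 1.96² × 0.25 / 0.01 = 96.04, rounded up to 97, against 100 stated. Other values of p (0.6, 0.7, 0.8, 0.9) give 93, 81, 62 and 35, so only p = 0.5 fits. The stated figure reproduces.

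Half-width at n = 100: 1.96 × √(0.25/100) = 9.8 points at p = 0.5, 9.0 at p = 0.7 and 7.8 at p = 0.8. With 110 per group and 10% lost, 99 remain (±9.85 points). These margins hold for a cutoff fixed before the data are seen.

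**2. Simulation of the plan as written.** 100 DED and 100 non-DED patients, MBI normal with equal variance in both groups, 4,000 replicates per scenario. Assumed AUC 0.60 to 0.90. Because the article does not say how the two measures are jointly maximised, two criteria were run: the largest sum of sensitivity and specificity (Youden) and the ROC point closest to the upper left corner. Apparent accuracy is compared with true accuracy at the cutoff actually chosen.

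Youden index (sensitivity + specificity − 1), MBI alone, Youden criterion. The best attainable value is 2Φ(δ/2) − 1 with δ = √2 Φ⁻¹(AUC):

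| AUC | Apparent | True at chosen cutoff | Difference | Best attainable |
|---|---|---|---|---|
| 0.70 | 0.338 | 0.275 | 0.063 | 0.289 |
| 0.76 | 0.426 | 0.369 | 0.057 | 0.383 |
| 0.90 | 0.667 | 0.624 | 0.043 | 0.635 |

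The average apparent value exceeds even what the best cutoff could achieve. The closest-to-corner criterion at AUC 0.70 gives 0.330 against 0.286, a difference of 0.044.

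**3. Optimism per measure, in percentage points.**

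| Scenario | Sensitivity | Specificity |
|---|---|---|
| MBI alone, Youden | +2.4 to +4.0 | +1.9 to +3.4 |
| MBI alone, closest to corner | +1.9 to +2.7 | +1.4 to +2.1 |
| MBI with J-OSDI, Youden, AUC 0.65 to 0.90 | +2.3 to +3.4 | +0.8 to +2.1 |

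The third row assumes that 95% of DED and 40% or 70% of non-DED patients reach the J-OSDI threshold. For example, at AUC 0.80 with 40%, sensitivity is 0.700 apparent against 0.672 true, and specificity 0.901 against 0.891.

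**4. Coverage of nominal 95% Wald intervals, MBI alone, for true performance at the chosen cutoff.** Youden: 86 to 90% per measure, 76 to 80% for both. Closest to corner: 90 to 93% per measure, 82 to 85% for both; a further run reached 86% jointly. With a fixed cutoff, per-measure coverage is 93 to 95%.

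**5. Distance from the truth at the chosen cutoff.** The estimate lies within ±10 points in 91 to 99% of replicates per measure, against 97 to 99.9% with a fixed cutoff.

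**6. A different target: accuracy at the population-optimal cutoff.** The spread (1.96 SD) of reported sensitivity is ±33, ±17 and ±12 points at AUC 0.60, 0.80 and 0.90 under Youden, and ±14, ±10 and ±8 under closest-to-corner.

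**The case against.** The strongest reply is that the effect is modest and the study is open about it. Deriving the cutoff is a declared aim, no performance goal or hypothesis test is attached to sensitivity or specificity, and 1 to 4 points cannot reverse a pass or fail decision. The cutoff is optimised on MBI alone while the primary rule also requires J-OSDI, which dampens the optimism in specificity. All of this stands and limits the weight of the point, but the bias remains: it was upward in every scenario run.

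A second reply is that the article names no interval method. This also stands in part. In the composite runs at AUC 0.80 and 0.90, Clopper-Pearson intervals covered 93 to 94% for sensitivity and 95 to 97% for specificity. A conservative interval hides part of the loss, but it does not remove the bias in the estimate.

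A third is that internal validation may be set out in an analysis plan that is not shown. The point does not rest on that silence: the article itself fixes how the cutoff is chosen, in whom, and that the primary accuracy is calculated with it.

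A reader might go further and infer that ±10% precision is not delivered and that the intervals are far too narrow. Under Youden at AUC 0.70 the SD of reported sensitivity is 0.119, so 1.96 × 0.119 is about ±23 points, and binomial intervals cover sensitivity at the population-optimal cutoff only about 53% of the time. The documents do not support that as the finding. Primary Outcome defines accuracy at the cutoff this study selects, not at the population-optimal one, and neither the criterion nor the AUC is given. Much of that spread is the cutoff moving along the ROC curve, trading sensitivity against specificity. The Discussion's interest in an optimal cutoff makes that target worth reporting, but it is not the primary outcome.

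**Conclusion.** The point holds in a limited form. As written, the plan overstates the primary sensitivity and specificity by about 1 to 4 points each. Nominal 95% Wald coverage at the chosen cutoff falls to about 86 to 93% per measure and roughly 76 to 86% jointly. The sample size calculation is arithmetically sound for a fixed cutoff, and its nominal half-width of at most 9.8 points is still met; what is lost is the 95% assurance attached to it.

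The sizes rest on normal, equal-variance MBI, assumed AUC 0.60 to 0.90, assumed J-OSDI pass rates and 100 patients per group. Balance is planned but not guaranteed, because groups form after enrollment, with "patients allocated into a DED group or a non-DED group based on the diagnosis obtained using the" standard method. At 150 against 50 patients (AUC 0.70 and 0.80, Youden, MBI alone), optimism in the measure from the smaller group rises to 4.6 to 5.8 points and its Wald coverage falls to 84 to 85%.

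**What to change.** Keep the ROC-derived cutoff, and before database lock specify that:

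- the selection criterion is named;
- the primary sensitivity and specificity of the full composite rule are reported after bootstrap optimism correction or repeated cross-validation, with the cutoff re-selected in every resample;
- the 95% CIs come from a procedure that repeats that selection;
- the ±10% figure is described as applying to a fixed cutoff.

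This needs analysis wording and a few lines of code, and no extra patients. The price is slightly lower accuracy figures and wider intervals. Correction is not complete: in a check at AUC 0.76 (400 replicates, 200 bootstraps each) the apparent Youden index was 0.428, corrected 0.388 and true 0.368, so 0.020 of the 0.060 optimism, a third, remained. Coverage of the corrected interval at the chosen cutoff was not established here and should be checked by simulation when the method is fixed.

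Splitting the sample is less attractive: 50 per group for testing gives ±13.9 points at p = 0.5 and ±11.1 at p = 0.8. Accuracy at the earlier slit-lamp-derived cutoff, whose value the article does not give, is an optional sensitivity analysis only.

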Secondary outcomes 1 to 4 were set to evaluate the DED diagnosis accuracy of the *test method* compared with that of the *standard method*. Secondary outcome 5 was included to determine the cutoff value for the app-based MBI using ROC analysis for DED diagnosis. Secondary outcomes 6 and 7 were included to determine if MBI measurements could be used as a substitute for TFBUT measurements. Secondary outcomes 8 and 9 were set to evaluate the reliability and validity of the app-based J-OSDI. Secondary outcomes 10 to 12 were set to evaluate the validity of app-based and slit lamp–based MBIs. In secondary outcome 13, patients will answer the following questions: “I think it’s easy to operate this smartphone app,” “I can use this smartphone app by myself,” “I want to be tested using this smartphone app rather than being tested at a medical institution,” and “I will continue to use this smartphone app” [49,50]. Patients will answer these questions on a 5-point Likert scale (1, strongly disagree; 2, disagree; 3, neutral; 4, agree; and 5, strongly agree) [51]. Secondary outcomes 14 and 15 were set to evaluate the safety and stability of the DEA01. DEA01 failure is defined as something not working as expected. Adverse events comprise unexpected signs, symptoms, or diseases encountered during the clinical trial, regardless of whether they are related to treatment. If serious adverse events or failure occur, these will be referred to the Juntendo Hospital Certified Review Board, and appropriate treatments will be provided as needed.

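### On its natural reading, the plan picks the MBI cutoff from an MBI-alone ROC curve, but the primary outcome uses that cutoff only together with app J-OSDI ≥13

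*Protocol article*

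**What the plan says.** All places are in the Protocol article, Methods.

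- **Primary Outcome.** A patient is test-positive with "an app-based J-OSDI total score ≥13 measured using the DEA01 and an MBI score" beyond the cutoff taken from secondary outcome 5. Both parts are required. The standard method is also a two-part rule: paper J-OSDI ≥13 and TFBUT ≤5.0 s.
- **Secondary Outcomes.** "Secondary outcome 5 was included to determine the cutoff value for the app-based MBI using ROC analysis for DED diagnosis". J-OSDI is not mentioned in that explanation. The list of outcomes, however, describes outcome 5 as a cutoff belonging to the test method.
- **Sample Size and Statistical Analyses.** The cutoff is "The point at which the sensitivity and specificity for DED diagnosis using the app-based MBI will be maximized". The same paragraph refers to diagnosis with the DEA01 when it means the whole test, so naming the MBI here appears deliberate.
- **Same section, on the AUC.** Performance is assessed by "calculating the area under the ROC curve plotted from the sensitivity and specificity of the" test method. The quantity varied to draw that curve is not named.
- **Discussion.** Establishing an optimal MBI cutoff for the app is presented as a main aim.

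**The concern.** DED under the standard method needs symptoms and a short TFBUT. If the MBI alone is run against that diagnosis, a patient with unstable tears but few symptoms counts as an MBI false positive, and such patients pull the cutoff towards strictness. In the test actually evaluated, most of them are already negative because their app J-OSDI is below 13. A cutoff made strict to exclude them then also removes true cases and gains less specificity than the MBI-alone curve suggested.

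What is at stake is the product of the study: the cutoff placed in an app meant to find undiagnosed patients. A similar ambiguity affects secondary outcome 4. An AUC computed from the final yes/no result would only restate the primary outcome.

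**Working it through.** **1. The plan's own figure.** The precision target is ±10% and "the confidence coefficient will be set at 95"%. The formula is not visible; assuming the usual n = z²p(1−p)/d² with p = 0.5, n = 1.96² × 0.25 / 0.01 = 96.04, so 97. This agrees with the plan: "the minimum sample size will be 100 patients in each group". Adding 10% gives 110. The present point leaves the sample size unchanged.

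**2. Direction, without simulation.** Take short MBI as positive. Let f_D and f_N be the MBI densities in DED and non-DED, and a_D(c), a_N(c) the probabilities of app J-OSDI ≥13 given MBI = c in each group.

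- MBI alone: Youden J is maximal where f_D(c) − f_N(c) = 0, so f_D/f_N = 1.
- Two-part rule: J is maximal where f_D(c)·a_D(c) − f_N(c)·a_N(c) = 0, so f_D/f_N = a_N/a_D.

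Every DED patient has paper J-OSDI ≥13 by definition. If the app score tracks the paper score, a_N/a_D is below 1. If f_D/f_N falls as MBI lengthens, the two-part optimum lies at a longer, more lenient MBI. The MBI-alone cutoff is therefore at least as strict. The two coincide as a_N approaches a_D, that is, when nearly everyone is symptomatic.

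**3. Size, under stated assumptions.** The documents give no J-OSDI, MBI or TFBUT distributions. A latent-normal model was used with app–paper J-OSDI correlation 0.9, MBI–TFBUT correlation 0.3, 0.5 or 0.7, and symptom–TFBUT correlation 0 or −0.3 (more symptoms with shorter TFBUT).

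One scenario with near-equal groups (DED 49%): 70% with J-OSDI ≥13, 70% with short TFBUT, MBI–TFBUT correlation 0.5, symptom–TFBUT correlation 0.

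| Cutoff chosen on | MBI percentile | Se of two-part test | Sp | J = Se + Sp − 1 |
|---|---|---|---|---|
| MBI alone | 54th | 0.585 | 0.821 | 0.406 |
| Two-part rule | 82nd | 0.811 | 0.660 | 0.471 |

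Loss in J = 0.471 − 0.406 = 0.065: sensitivity is 0.811 − 0.585 = 0.226 lower and specificity 0.821 − 0.660 = 0.161 higher.

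With DED held at about 50%, the loss in J by share with J-OSDI ≥13 is:

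| Share with J-OSDI ≥13 | Loss in J |
|---|---|
| 65% | 0.05–0.15 |
| 75% | 0.03–0.08 |
| 85% | 0.00–0.03 |
| 95% | about 0 |

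In a second grid of 18 scenarios (60–80% symptomatic, DED share 48–67%) the loss was 0.03–0.22. The largest value came at 60% symptomatic with MBI–TFBUT correlation 0.3. At 80% symptomatic with DED at 64–67% it was 0.03–0.10, so the table above holds only for DED near 50%.

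**4. AUC.** A single operating point joined by straight lines to the corners has area (Se + Sp)/2. In the example that is (0.585 + 0.821)/2 = 0.703. Varying the MBI with J-OSDI fixed at ≥13 gives 0.796. Over the 18 scenarios the two differ by 0.07–0.14.

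**The case against.** - **Stand-alone tuning is not stated outright.** Outcome 5 is listed as a cutoff of the test method, and the analysis section also speaks of the cutoff in the test method. Both fit a sweep inside the two-part rule. This stands: MBI-alone tuning is the natural reading, not the only one.
- **A reader might infer that the test-method AUC rests on one operating point.** The article does not say so. Varying the MBI with J-OSDI fixed would give a multi-point curve. What remains is that the varied quantity is unnamed.
- **A reader might infer that no cutoff criterion exists, because sensitivity and specificity cannot in general both be maximal at one point.** The wording is loose, but the section cites an earlier study for the method, and the exact criterion may sit there or in the full plan. This is not pressed.
- **A reader might infer biased accuracy estimates.** A non-optimal cutoff does not bias the sensitivity and specificity of the test that uses it. Choosing and evaluating the cutoff in the same patients is a separate matter.
- **The effect may be small.** Patients have DED or suspected DED, so a high symptomatic share is plausible, and the loss then shrinks towards zero. This stands.
- **The alternative has its own weakness.** With 65% symptomatic and MBI–TFBUT correlation 0.3, the two-part optimum falls at about the 97th–98th MBI percentile, so the MBI almost drops out. Tuning the MBI on its own signal is a defensible secondary aim. This stands, and is a reason to report both.

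**Conclusion.** The point holds in a limited form. As naturally read, the cutoff is optimised for the MBI alone and then used in a two-part rule for which it is generally not optimal. The direction, towards strictness, follows from the definitions if the app and paper questionnaires agree reasonably and short MBI indicates DED. The size is not known from the documents. For DED near 50% it ranges from about 0 (nearly all symptomatic) through 0.03–0.08 (75%) to about 0.15 (65%) on the Youden scale. This is a net figure: lower sensitivity is partly repaid by higher specificity.

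The documents do not support saying that the two-part test will do worse than the questionnaire alone. That occurred in 14 of 24 assumed scenarios in one set of runs, so it is a possibility that depends on the inputs. The consequence that can be supported is that the delivered cutoff need not be the optimum for the app as it will be used, and that the text should say which test it is optimised for.

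**What to change.** 1. **Reconcile the direction first.** The Primary Outcome counts an MBI above the cutoff as positive, whereas the Introduction and Discussion report a positive MBI–TFBUT correlation, which would pair short MBI with short TFBUT. These places must be made consistent before any cutoff is derived.
2. **Sample Size and Statistical Analyses, cutoff.** State that c is selected by sweeping the MBI within the rule app J-OSDI ≥13 AND app MBI beyond c, against the standard method, and taking the c that maximises the Youden index of that rule. Align the description of secondary outcome 5.
3. **MBI-alone ROC and cutoff.** Keep them as descriptive results and for secondary outcomes 6 and 7 (TFBUT ≤5.0 s).
4. **Secondary outcome 4.** State that the MBI is varied with J-OSDI fixed at ≥13. A model-based combined score is optional and would evaluate a different test.

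Cost: wording and a few lines of code, with no extra patients or data. Downside: the cutoff is specific to its pairing with J-OSDI ≥13. If the MBI is weakly informative, the optimum may be so lenient that the MBI adds little; this should be reported beside the MBI-alone result.

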## Introduction

Dry eye disease (DED) is one of the most frequently encountered ocular surface diseases, with a prevalence ranging from 5% to 50% [1,2], which is projected to increase, likely due to the worldwide trend toward an aging population and lifestyle changes associated with a digitalized society [1-4]. DED-related symptoms are detrimental to quality of life (QoL) and work productivity, leading to society-wide economic loss [5,6]. Subjective DED-related symptoms are highly variable and include ocular dryness, eye discomfort, eye strain, decreased visual acuity, and photophobia [7-11]. Additionally, DED is highly heterogeneous, with patients presenting with seemingly unpredictable combinations of the abovementioned symptoms. Therefore, patients with DED are prone to having their nonspecific presentations overlooked, and many are left undiagnosed without appropriate management [3,9,12-14]. There is no definitive cure for DED, and current standards of care comprise ex post facto symptom management, highlighting the importance of early diagnosis and intervention to prevent disease progression and longstanding damage [15-19].

Concerning DED diagnosis, Tear Film & Ocular Surface Society and Asian Dry Eye Society criteria recommend evaluating a patient’s subjective symptoms and tear film breakup time (TFBUT) [20,21]. However, TFBUT measurement is inherently invasive owing to the need for sodium fluorescein application, and measurements under light microscopy are required [20-23]. The ongoing COVID-19 pandemic has also increased the demand for a noninvasive alternative that could be used in remote settings [24,25]. One major obstacle to DED diagnosis in the context of telemedicine is the inability to evaluate the ocular surface and the use of slit-lamp microscopy in TFBUT, and clinicians may be solely reliant on subjective symptoms for diagnosis. Therefore, identification of a novel proxy for existing invasive examinations is needed for a reliable, noninvasive DED diagnosis.

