This study may have some limitations. First, this study may be affected by selection bias, as study patients are limited to those who have been evaluated in a highly specialized university hospital and those who are able to use the smartphone app [32]. Second, the study will be performed in a specific order. Patients will be required to first use the app, after which there will be a clinical evaluation for DED. This study sequence may be a confounder and might affect the results; therefore, assessing the effects of the examination order in a randomized study may be necessary [61]. Lastly, the DEA01 is designed to be an ancillary tool for initial DED diagnosis assistance, and specialized tests such as corneal staining and Schirmer test may be required to further assess disease severity and progression.

In conclusion, this study will evaluate the capability of the DEA01 in assisting a DED diagnosis. The study findings may potentially help to establish a noncontact, noninvasive, and remote consultation method for app-based DED diagnostic assistance using the mHealth DEA01 smartphone app. It is hoped that the DEA01 will provide effective diagnostic evaluation for DED in telemedicine and allow for early intervention in patients who have not been diagnosed with DED due to limited access to medical care.

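### PPV, NPV and concordance read from the study's own 2x2 table hold only for the study's DED share; PPV is overstated wherever DED is less common among the app's intended users

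*Protocol article*

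**What the plan says.** Secondary Outcomes lists the overall concordance rate, the positive and negative predictive values and the likelihood ratios. Sample Size and Statistical Analyses fixes how they are obtained: "positive/negative predictive value, and positive/negative likelihood ratio will be calculated by comparing the DED diagnosis results from the" test method with those from the standard method in one cross-table. It mentions no target prevalence and no limit on what the predictive values apply to.

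Two things bear on the DED share in that table:

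- The sample size section derives a minimum per group ("Therefore, the minimum sample size will be 100 patients in each group") and then states that "the target total number of patients will be set at 110 for each group", "assuming a 10% exclusion rate due to missing data".
- Study Design describes a minimum of 220 patients, "with patients allocated into a DED group or a non-DED group based on the diagnosis obtained using the" standard method. Patient Selection and Textbox 1 restrict entry to ophthalmology outpatients at the participating hospitals who have DED or suspected DED. No quota or group-wise stopping rule is described.

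On intended use, the Abstract calls the app a remote screening device, and the Discussion hopes it will "allow for early intervention in patients who have not been diagnosed with DED due to limited access to medical care". The Introduction describes DED as a common disease "with a prevalence ranging from 5% to 50" per cent.

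**The concern.** Sensitivity, specificity and likelihood ratios do not depend directly on how common the disease is in the sample. PPV and NPV do, and so does the concordance rate whenever sensitivity and specificity differ. Here the DED share in the table is set either by a precision target for sensitivity and specificity or by the case mix of eye clinics in hospitals that the Discussion itself calls highly specialised. Neither source represents undiagnosed people using an app at home.

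PPV is the figure a user or telemedicine clinician will read as the chance that a positive result is right. If the study reports it only at its own DED share, and the users' prevalence is lower, they will trust a positive result more than they should. NPV errs the other way, so a negative result looks less reassuring than it would be.

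**Working it through.** **Inputs from the protocol.** Target 110 DED and 110 non-DED; minimum 100 per group; 10% exclusion; CI half-width of 10 points for sensitivity and specificity; 95% confidence; disease prevalence 5% to 50%.

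**Input assumed.** The protocol gives no expected sensitivity (Se) or specificity (Sp). I take Se = Sp = 70%, 80% and 90%.

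**Step 1: the plan's own figure.** Formula (2) is not shown in the text at hand, so I use the usual precision formula with p = 0.5:

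- n = z² p(1−p)/d² = 1.96² × 0.25/0.10² = 96.04, so 97 per group. With z rounded to 2, n is exactly 100.
- 100 × 1.10 = 110 per group. Dividing by 0.90 would give 112, a difference of 2.

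The stated 100 and 110 are reproduced. The targeted DED share is 110/220 = 50%, and it follows from precision for Se and Sp, not from epidemiology.

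**Step 2: PPV at other prevalences.** With prevalence π,

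PPV = Se·π / [Se·π + (1−Sp)(1−π)].

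Example, Se = Sp = 80%, π = 10%: 0.08/(0.08 + 0.18) = 0.31. At π = 50% it is 0.40/(0.40 + 0.10) = 0.80. Ratio: 0.80/0.308 = 2.6.

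PPV, with the ratio of the 50%-share PPV to it in brackets:

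| Prevalence | Se = Sp = 70% | 80% | 90% |
|---|---|---|---|
| 50% | 0.70 (1.0) | 0.80 (1.0) | 0.90 (1.0) |
| 30% | 0.50 (1.4) | 0.63 (1.3) | 0.79 (1.1) |
| 20% | 0.37 (1.9) | 0.50 (1.6) | 0.69 (1.3) |
| 10% | 0.21 (3.4) | 0.31 (2.6) | 0.50 (1.8) |
| 5% | 0.11 (6.4) | 0.17 (4.6) | 0.32 (2.8) |

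**Step 3: where the excess becomes large.** For Se = Sp = s and a 50% share, the ratio is s + (1−s)(1−π)/π. Setting it to 3 gives π = (1−s)/(4−2s): 0.3/2.6 = 11.5%, 0.2/2.4 = 8.3% and 0.1/2.2 = 4.5% for s = 70%, 80% and 90%. Setting it to 2 gives π = (1−s)/(3−2s): 18.8%, 14.3% and 8.3%.

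**Step 4: NPV.** NPV = Sp(1−π) / [Sp(1−π) + (1−Se)π]. At Se = Sp = 80% it is 0.80 at a 50% share, 0.72/(0.72 + 0.02) = 0.97 at 10%, and 0.99 at 5%.

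**Step 5: concordance.** Concordance = Se·π + Sp(1−π). It is constant when Se = Sp. With Se = 90% and Sp = 70% it is 0.80 at 50% and 0.72 at 10%; with the two reversed it is 0.80 and 0.88.

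**Step 6: if the realised share is not 50%.** A higher share, possible when entry requires known or suspected DED, widens the gap. At a 70% share and Se = Sp = 80%, the table PPV is 0.90 and the table NPV 0.63.

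**The case against.** The best case for leaving the plan alone has five parts.

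1. *The table values are valid for the patients recruited.* This stands. In a prospective cross-sectional sample the cross-table estimates PPV and NPV for that population. The issue is only their transfer to other users.
2. *The reader already has what is needed.* Sensitivity and specificity are primary, likelihood ratios are secondary, and the Discussion admits selection bias from specialised hospitals. This softens the point but does not remove it. The predictive values that the plan will produce are the unadjusted ones, and the limitation is not linked to them.
3. *PPV and NPV are secondary and descriptive, with no decision attached.* True. The primary outcome is unaffected.
4. *A condensed article may leave prevalence-standardised values to the analysis plan.* It may, but this article does not leave the method open. It states how the values are calculated.
5. *Bayes' rule has its own weakness.* It assumes that Se and Sp from suspected-DED hospital patients carry over to undiagnosed people. They may also be optimistic, because the MBI cutoff is chosen on the same data. This stands and must accompany any restated table.

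A reader might go further and infer that the reported PPV will be several times too favourable for the undiagnosed population. The documents do not support that. A threefold excess needs prevalence at or below roughly 4.5% to 11.5%, depending on accuracy, and the protocol gives no prevalence for app users. Its 5% to 50% describes the disease in general, and the targeted 50% lies inside that range. Nor is a 50:50 quota described: 110 per group is a target, and patients are classified after enrolment.

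**Conclusion.** The point holds as a limit on what the planned predictive values and concordance rate mean. They are specific to the study's DED proportion, and the plan neither says so nor restates them for the use it promotes. The direction is certain for any informative test: where users' prevalence is below the study share, the table PPV is too high and the table NPV too low.

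The size depends on figures the protocol does not give, and ranges from no excess to the more than sixfold excess at the low end of the quoted disease prevalence. At 20% prevalence and 80% accuracy, a positive result would be right half the time, where the table would say four times in five. These figures rest on a realised 50% share, equal and assumed Se and Sp, and their transfer to the new population. The change is worth making, but the study's design and primary analysis do not depend on it.

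**What to change.** In Sample Size and Statistical Analyses:

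- Keep PPV, NPV and concordance from the cross-table, but label them as specific to the study's observed DED proportion, and report that proportion beside them.
- Add PPV and NPV computed by Bayes' rule from the estimated sensitivity and specificity at stated prevalences across the quoted range, for example 5%, 10%, 20%, 30% and 50%, with 95% confidence intervals (a bootstrap would serve).
- State under that table that it assumes sensitivity and specificity carry over from hospital patients with known or suspected DED, and that both may be optimistic because the MBI cutoff is chosen on the same data.

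The cost is one extra table and a footnote, with no new data and no change to the sample size. The downside for the sponsor is a less favourable PPV at the lower prevalences.
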